## Abstract

**Background:**

Mild cognitive impairment (MCI) is the predementia phase of Alzheimer’s disease (AD). The intestinal microbiome is altered in MCI and AD, and apolipoprotein E (*ApoE*) ε4 gene polymorphism is a risk factor for the progression of MCI to AD. This study aims to investigate the improvement in cognitive function of MCI patients with and without *ApoE* ε4 due to acupuncture and the changes in gut microbiota community composition and abundance in MCI.

**Methods:**

This randomized assessor-blind controlled study will enrol MCI patients with and without the *ApoE* ε4 gene (n = 60/60). Sixty subjects with the *ApoE* ε4 gene and 60 subjects without the *ApoE* ε4 gene will be randomly allocated into treatment and control groups in a 1:1 ratio. Intestinal microbiome profiles will be evaluated by 16 S rRNA sequencing of faecal samples and compared between the groups.

**Results/conclusions:**

Acupuncture is an effective method to improve cognitive function in MCI. This study will provide data on the relationship between the gut microbiota and the effectiveness of acupuncture in patients with MCI from a new angle. This study will also provide data on the relationship between the gut microbiota and an AD susceptibility gene by integrating microbiologic and molecular approaches.

**Trial registration:**

www.chictr.org.cn, ID: ChiCTR2100043017, recorded on 4 February 2021.

## Introduction

Mild cognitive impairment (MCI) is a clinical state between normal ageing and Alzheimer’s disease (AD) that does not meet the definition of dementia. It is characterized by a gradual decline in memory or other cognitive functions that does not affect activities of daily living (ADL) [1]. The prevalence of MCI increases with age, from 6.7% at 60–64 years to 25.2% at 80–84 years [2]. The prevalence of MCI in China in the population aged > 65 years old is 15.5% [1]. MCI constitutes a major health care burden for society, with the global cost in 2010 estimated at over 6 trillion US dollars [3].

Apolipoprotein E (ApoE) is a plasma protein that regulates cholesterol balance and the metabolism of lipoproteins in the nervous system [4]. The 3 isoforms of ApoE—ApoE2, ApoE3, and ApoE4—differ by 1 or 2 amino acid residues but have markedly different effects on AD risk: *ApoE2*, which has an allele frequency of ~ 8%, is known to be neuroprotective, whereas *ApoE4* has a prevalence of approximately 14% and is one of the strongest risk factors for AD [5–7]. The *ApoE* ε4 allele has been widely studied as a risk factor for MCI and AD [8, 9]. The lifetime risk of developing AD at the age of 85 years is 65% for individuals with 2 copies of the *ApoE* ε4 allele, compared with 10% for those with the ε3/ε3 genotype [10].

The aetiology of AD is multifactorial, and pathologic changes such as the accumulation of amyloid β and tau proteins occur years before the onset of signs and symptoms [11]. The *ApoE* ε4 allele has been implicated in AD pathogenesis [12], but multiple gene variants may have combinatorial effects on AD susceptibility. One study found that the presence of *ApoE* ε4 was associated with a lower Mini-Mental State Examination (MMSE) score but only in subjects with a substantial iron homeostasis gene burden [13].

In the management of dementia, early intervention in MCI is key [14]. Acupuncture is widely used to improve the clinical symptoms and delay the progression of MCI [15], as there are no appropriate drug treatments [2].

The complexity and multifactorial aetiology of AD pose unique challenges to studying its pathogenesis and developing treatment methods. Various pathological changes occur several years before the first appearance of symptoms [11]. Increasing evidence suggests that the gut microbiota is also involved in memory formation, processing, and storage [16]. Intestinal microorganisms are thought to contribute to the pathology of neurodegenerative diseases via the gut–brain axis [17–19] according to the observation that gut microbiota community composition and abundance are altered in patients with AD [18, 20, 21]. Intestinal flora can be readily isolated from faecal samples.

The study of intestinal flora and the gut–brain axis can potentially reveal novel diagnostic biomarkers for AD [17, 20, 22], but there is conflicting evidence regarding the relationship between the *ApoE* ε4 polymorphism and the gut microbiome profile. One study reported that differences in gut microbiota communities at the genus level between AD patients and normal subjects were not correlated with the *ApoE* genotype [20]. On the other hand, using the common voxel-based specific regional analysis system for AD scores, it was demonstrated that cortical and hippocampal atrophy was associated with changes in gut flora composition and abundance and *ApoE* polymorphism in MCI patients [23].

Although studies on the gut microbiota and acupuncture are lacking, the discovery of the partial relief of dysbiosis in the gut microbiome in MCI by acupuncture [24] has aroused great interest among researchers. Additionally, genetic markers that predict the progression of MCI are needed so that interventions to prevent AD development can be implemented. To this end, the proposed study will investigate the relationship between *ApoE* gene polymorphisms and the intestinal microbiome profile in patients with MCI. Exploring the evolution process of the intestinal microbiome of patients carrying different genes before and after acupuncture can provide more research data to reveal the relationship between the gut microbiota and neurodegenerative diseases.

## Methods

### Study design and population

This single-centre, randomized, assessor- and data analyst-blind controlled study will include 2 groups of patients—those with and without *ApoE ε4* gene polymorphism (n = 60/group)—recruited from the outpatient department of Zhejiang Hospital. Each group of patients will be randomly assigned to the acupuncture group or the sham acupuncture group. The study protocol was approved by the Ethics Committee of Zhejiang Hospital (2021-LS-12 K) on January 25, 2021. Each participant and/or their guardian will be informed of the nature of the study by telephone and will be required to sign the informed consent form before enrolment, which will take place from March 2021 to December 2022. Data will be analysed, and the results will be published in 2023. The proposal is depicted in Fig. 1.

**Fig. 1 Fig1:**
[figure not shown]
Study flow chart

### Inclusion and exclusion criteria

The patient inclusion criteria, as defined according to our previous research [25], are as follows: (1) confirmed diagnosis of MCI; (2) deficits in ≥ 1 cognitive domains as determined by objective examination; (3) Clinical Dementia Rating score of 0.5; (4) normal ADL score; (5) MMSE score ≥ 24 but ≤ 28 and Geriatric Depression Scale (GDS) score < 9; (6) stable and reliable caregivers; (7) aged ≥ 60 years; and (8) provision of informed consent. The exclusion criteria [25] are as follows: (1) age < 60 years; (2) diagnosed with any type of dementia; (3) comorbid acute and chronic cerebrovascular disease, encephalitis, Parkinson’s disease, leukoencephalopathy, and other central nervous system diseases; (4) hypothyroidism, vitamin B12 deficiency, depression, syphilis, and other conditions that may affect cognitive decline; (5) GDS score ≥ 9; (6) severe hearing and visual impairment or inability to complete neuropsychologic tests; (7) liver and kidney dysfunction or haematopoietic system disorder; (8) use of antibiotics and probiotics within 1 month before enrolment; and (9) inflammatory gastrointestinal diseases, irritable bowel syndrome, chronic constipation, chronic diarrhoea, *Helicobacter pylori* infection (untreated), and other diseases affecting the intestinal flora.

### Sample size estimation

Using GPower 3.1.9.6 to determine the sample size, a single-factor ANOVA was selected for prior analysis at the 4-group level, with a response size of 0.4, a test level of 0.05, a test efficacy of 0.9, a sample size of 96, and a 25% dropout rate. The final sample size was determined to be 120 people, with 30 people in each group, which was similar to that of other studies [20, 26, 27]. The necessary number of participants was recorded at baseline. Before the end of the enrolment period, more patients will be recruited to replace those who were excluded after baseline examinations.

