### Data analysis

Measurement data will be expressed as the means ± standard deviations, and count data will be expressed as frequencies. Data will be analysed using SPSS Statistics for Windows v21 (IBM, Armonk, NY, USA). Pearson’s χ2 test or Fisher’s exact test will be used to analyse classified variables. The t test will be used if the normal distribution and homogeneity test are satisfied, and the rank sum test will be used for nonnormality or nonuniformity of variance. The Kruskal‒Wallis test will be used for multigroup comparisons, and the Wilcoxon rank sum test will be used for comparisons between two samples. For repeated measurement data, repeated measurement analysis of variance will be used. For the pairwise comparison of multiple groups of data, the Bonferroni method will be used to adjust the test level.

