## Discussion

MCI is the prophase state of dementia and the key phase for early intervention. At present, there is no drug that can be used in the MCI stage. Acupuncture reflects the value of early intervention in MCI. The purpose of this study is to evaluate the difference in the curative effect of acupuncture on MCI patients with and without the *ApoE ε4* gene polymorphism and to explore the relationship between the acupuncture mechanism and changes in the intestinal flora. We hope to be able to provide assessable biomarkers associated with acupuncture treatment.

*ApoE* ε4 is associated with degeneration of brain capillary pericytes that maintain blood–brain barrier (BBB) integrity [8, 41]. *ApoE* ε4 carriers (ε3/ε4 or ε4/ε4 alleles) are distinguished from noncarriers (ε3/ε3) by BBB breakdown in the hippocampus and medial temporal lobe [8]. Disruption of the gut flora balance in pathogen-free mice has been linked to increased BBB permeability in the embryonic stage of development and in adults [42] as well as central nervous system abnormalities such as cortical myelination, hippocampal neurogenesis, cognitive function, and memory formation [43]. It has been suggested that systemic inflammation induced by compounds secreted by bacteria impairs the BBB and promotes neurodegeneration [44–46]. We hypothesize that specific types of microbiota contribute to *ApoE* ε4-associated breakdown of the BBB in patients with MCI and can serve as biomarkers for progression to AD.

EX-HN1 (Sishencong) and GV20 (Baihui) have the local effect of regulating brain function. Acupoints can regulate the brain network by increasing connections between cognitive-related regions, thereby improving cognitive function in MCI patients [47]. By improving brain function, acupoints further affect the movement, sensation, and secretion of the gastrointestinal tract through the descending pathway of the gut–brain axis and regulate the composition and behaviour of the gut microbiota [48]. The purpose of our research is to elucidate the relationship between acupoints and gut microbiota.

Clinically, acupuncturists treat patients individually based on their symptoms. As the fixed acupuncture program can reduce research deviation and is more conducive to promotion, we selected fixed acupoints.

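### The stated 0.9 power belongs to an omnibus four-group test: power for acupuncture versus sham is not established, and power for the ApoE ε4 difference is at most 0.78 at f = 0.4 unless effects run in opposite directions

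*Protocol article*

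**What the plan says.** The protocol article, Sample size estimation, reports that "a single-factor ANOVA was selected for prior analysis at the 4-group level, with a response size of 0.4, a test level of 0.05". The target power is 0.9, reached with 96 evaluable patients. A 25% dropout allowance then brings the total to 120, or 30 per group. The section gives no MoCA difference, SD or cell means, and no calculation for any particular contrast.

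The Abstract (Methods) and Study design describe a 2 × 2 layout: 60 ApoE ε4 carriers and 60 non-carriers, each randomised 1:1 to acupuncture or sham. Genotype is a stratum, not a randomised factor.

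On the aim, the Discussion says, with reference to the ApoE ε4 polymorphism: "The purpose of this study is to evaluate the difference in the curative effect of acupuncture on MCI patients with and without". The Abstract's aim is cognitive improvement from acupuncture in both genotype groups, together with microbiota changes. The Primary outcome section makes improvement in MoCA the main result.

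The Data analysis section lists t or rank-sum tests, Kruskal–Wallis and repeated-measures ANOVA, and adds: "For the pairwise comparison of multiple groups of data, the Bonferroni method will be used to adjust the test level". A single-factor ANOVA is not on that list.

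**The concern.** A one-way ANOVA on four groups has 3 numerator degrees of freedom and asks only whether the four means are all equal. In this 2 × 2 layout those degrees of freedom split into an acupuncture effect, a genotype effect and an acupuncture-by-genotype interaction. The trial's questions are the first and the third, each with 1 degree of freedom. The sizing covers all three together, so the 0.9 could be met entirely by a carrier versus non-carrier difference, which is not a randomised comparison and says nothing about acupuncture.

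The risk lies in interpretation. If 0.9 is taken as the power to detect a difference in acupuncture effect by genotype, a non-significant interaction may be read as showing that carriers and non-carriers benefit equally. For moderate differences, a non-significant interaction is the likelier result even when the difference is real.

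**Working it through.** **Inputs.** From Sample size estimation: f = 0.4, α = 0.05, power 0.9, N = 96 (24 per cell), 25% dropout, final N = 120. Ninety completers is 120 × 0.75. Assumptions: 0.4 is Cohen's f (the article calls it a response size), cells are equal, SD = 1, and there is one outcome comparison without baseline adjustment.

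**Step 1: reproduce the stated figure.** Noncentral F with λ = f²N and df = (3, N − 4).
- N = 92: λ = 0.16 × 92 = 14.72, power 0.898.
- N = 96: λ = 0.16 × 96 = 15.36, power 0.912.

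So 96 is the smallest balanced total that reaches 0.9. The arithmetic is right for the omnibus test. With 90 completers the power is 0.89.

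**Step 2: a genotype difference alone.** For two levels differing by d, f = d/2. With d = 0.8 SD between carriers and non-carriers and no acupuncture effect, f = 0.4, and the omnibus test rejects with the same probability, 0.91.

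**Step 3: split f into its components.** In a balanced 2 × 2 layout

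f² = (M/2)² + (G/2)² + (D/4)²,

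where M is the acupuncture effect averaged over strata, G is the genotype difference and D is the difference between the two stratum-specific acupuncture effects, all in SD units. Each component is tested with df = (1, N − 4) and λ = (component f)² × N.

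**Step 4: pooled acupuncture versus sham, N = 96.**

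| Share of f² = 0.16 due to M | M (SD) | Power |
|---|---|---|
| all | 0.80 | 0.97 (0.96 at 90 completers) |
| half | 0.57 | 0.78 |
| one third | 0.46 | 0.61 |
| none | 0 | 0.05 |

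Power of 0.9 needs a component f of 0.334 at N = 96, so M = 2 × 0.334 = 0.67 SD. With 90 completers it is 2 × 0.346 = 0.69 SD.

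**Step 5: difference in acupuncture effect by ApoE ε4, N = 96.**
- Power of 0.9 needs D = 4 × 0.334 = 1.34 SD, or 4 × 0.346 = 1.38 SD with 90 completers.
- D = 0.5 SD: power 0.23. D = 0.8 SD: power 0.49.
- Effect in one stratum only, the other three cells equal: f = 0.433d, so f = 0.4 gives d = 0.92 and D = 0.92. Power 0.61 (0.58 at 90 completers).
- Effect in one stratum half that in the other (0.48 and 0.97 SD, which also gives f = 0.4): power 0.22.
- Upper bound: if the two effects do not have opposite signs, D ≤ 2M, so D/4 ≤ M/2 and (D/4)² is at most half of f². Then D/4 ≤ √0.08 = 0.283, D ≤ 1.13 SD, and power is at most 0.78.
- Full crossover (+0.8 and −0.8 SD): D = 1.6, power 0.97.

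**Step 6: sensitivity to baseline adjustment.** If f = 0.4 is on the raw-score scale and the baseline–outcome correlation is assumed to be 0.5 to 0.7 (the article gives none), the residual SD falls by √(1 − ρ²), to 0.866 or 0.714. The 90% detectable D becomes 1.34 × 0.866 = 1.16 SD or 1.34 × 0.714 = 0.96 SD. Power in the one-stratum pattern rises from 0.61 to 0.73 or 0.88. The 0.78 bound also rises: 1.13/0.866 = 1.31 SD and 1.13/0.714 = 1.58 SD, with power about 0.89 and 0.97. If 0.4 already refers to the adjusted or change scale, nothing is gained.

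**The case against.** A reader might infer that the trial lacks 0.9 power for acupuncture versus sham as well. The documents do not support that. A 1-df test at the same f = 0.4 is more powerful than the omnibus test, with 0.97 against 0.91 if the whole effect is due to treatment. Without cell means, power for this contrast is unspecified, not shown to be low.

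The interaction is also not the trial's only question. The Abstract's aim and the Primary outcome section give acupuncture's effect on cognition at least equal prominence. That stands, but the Discussion names the difference by genotype as the study's purpose, so it needs its own power statement.

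The article names its test openly, its arithmetic is correct, and it never says that 0.9 applies to either contrast or that a null interaction would mean equal effect. The misreading is therefore a risk, not a claim the article makes. The article also calls the study a pilot. That softens the consequence but does not connect the 0.9 to the questions asked.

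It is tempting to quote low power for within-stratum pairwise tests: with 24 versus 24 and 0.8 SD, power is 0.77 unadjusted, 0.68 at 0.05/2 and 0.51 at 0.05/6. The article fixes Bonferroni but not the number of comparisons, so no single figure can be held against it.

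Finally, MoCA is measured at baseline and repeatedly afterwards, and repeated-measures ANOVA is planned. This could raise power, as Step 6 shows. The size of the gain cannot be established because no correlation is given, and the sizing did not use one.

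**Conclusion.** The point holds in limited form. The 0.9 is a true statement about the omnibus test (0.912 at N = 96), but it is not the power for either contrast the trial will interpret. For pooled acupuncture versus sham, power is not established and depends on cell means the article does not give. For the difference by ApoE ε4, power at f = 0.4 stays below 0.9 in every pattern where acupuncture does not act in opposite directions in the two strata. This last conclusion rests on an unadjusted single comparison, equal cells and 0.4 being Cohen's f. Under strong baseline adjustment on the raw-score scale it would weaken, although the one-stratum pattern would still fall short of 0.9 at the correlations tried.

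**What to change.** Keep N = 120. In Sample size estimation:

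1. Qualify the 0.9 as applying to the omnibus four-group test only. It need not be deleted, because it is correct for that test.
2. Add the differences detectable with 90% power: about 0.67 SD (96 completers) or 0.69 SD (90 completers) for the pooled acupuncture effect, and about 1.34 or 1.38 SD for the treatment × ApoE ε4 interaction.
3. State the assumptions with these figures: Cohen's f scale, equal cells, one comparison without baseline adjustment. If an adjusted analysis is intended, give the assumed correlation and its source.

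In Data analysis, state that the interaction will be reported as an estimate with a 95% CI and that a non-significant interaction is not evidence of equal effect in carriers and non-carriers.

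The cost is rewording and a less favourable stated power for the interaction. No extra patients are needed.

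### Enrolling 120 covers a 20% dropout from the required 96, not the stated 25%; at 25%, 90 remain and power is about 0.89 (minor arithmetic error)

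*Protocol article*

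**What the plan says.** All the figures are in the protocol article, Methods, Sample size estimation. The calculation was made in G*Power: "a single-factor ANOVA was selected for prior analysis at the 4-group level", "with a response size of 0.4", "a test level of 0.05". The results follow in the same sentence: "a test efficacy of 0.9, a sample size of 96, and a 25% dropout rate". The next sentence gives the enrolment target: "The final sample size was determined to be 120 people, with 30 people in each group".

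The section does not show how 96 became 120. It adds that the total resembles that of other studies. It also says that, while enrolment is open, further patients will be recruited in place of those excluded once baseline examinations are done. It says nothing about replacing participants who leave later.

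**The concern.** A dropout rate is a proportion of those enrolled. To finish with n evaluable participants when a fraction d is lost, one enrols n/(1 - d). Adding a fraction d on top of n, which is n x (1 + d), gives too few. Here 120 matches the second form and not the first.

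This is the article's only justification of the sample size. A reader will take it to mean that the trial can lose a quarter of its participants and still have 0.9 power. If that is not so, the stated dropout tolerance or the stated power is wrong as printed.

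**Working it through.** **Inputs, all from Sample size estimation:** 4 groups, equal allocation; effect size 0.4, read as Cohen's f; alpha 0.05; target power 0.90; 96 before dropout; dropout 25%; 120 enrolled.

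**Step 1: reproduce the 96.** Power = P(F' > F crit), where F' is noncentral F with 3 and N - 4 degrees of freedom and noncentrality N x f², and F crit is the central F quantile at 0.95.

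| N | Noncentrality (N x 0.16) | Power |
|---|---|---|
| 88 (22 per group) | 14.08 | 0.8824 |
| 90 | 14.40 | 0.8904 |
| 92 (23 per group) | 14.72 | 0.8979 |
| 93 | 14.88 | 0.9015 |
| 96 (24 per group) | 15.36 | 0.9115 |

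The smallest total reaching 0.90 is 93, and the smallest with equal groups is 96. The stated 96 is reproduced exactly, which also supports reading 0.4 as Cohen's f.

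**Step 2: the dropout allowance.**
- 96 x (1 + 0.25) = 120, the stated figure.
- 96/(1 - 0.25) = 128, or 32 per group.
- Starting instead from the unrounded minimum, 93/(1 - 0.25) = 124, or 31 per group. This is still more than 120.

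**Step 3: what 120 delivers at 25% dropout.**
- 120 x 0.75 = 90 remain, an average of 22.5 per group.
- 96 - 90 = 6 short of the stated number; 93 - 90 = 3 short of the minimum for 0.90.
- Power at 90 is 0.8904, about 1 percentage point below the 0.90 target and about 2 points below the 0.9115 that 96 would give.

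**Step 4: what dropout 120 can bear.**
- To keep 96: 1 - 96/120 = 20%.
- To keep 93, and so just reach 0.90: 1 - 93/120 = 22.5%.

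Both are below 25%.

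**The case against.** The strongest reply is that this hardly matters. Power of 0.8904 rounds to 0.9 at the precision the article uses. The gap to the target is one point, and 0.9115 is partly a bonus from rounding up to equal groups. The article offers no derivation of the effect size, so uncertainty about that assumption could easily outweigh one point of power. The Discussion calls the study a single-centre pilot, and the Results section reports 98 participants already enrolled. All of this stands, and it is why the point is minor.

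A second reply is that losses may be replaced. If the 25% includes patients excluded after the baseline examinations, replacing 3 of the 30 losses would reach 93, and replacing 6 would restore 96. The article does not say whether those exclusions are counted in the 25%. The rule does not extend to losses over the 12 weeks of treatment or in follow-up, so it cannot be relied on to close the gap.

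A third reply is that the article nowhere states a multiplication by 1.25, and it attaches 0.9 to 96 rather than expressly to what is left of 120. That is fair: the multiplication is an inference. But an allowance for dropout is normally there to protect the evaluable number, and 120 with 25% lost does not leave 96 whatever route led to it. If a 25% addition to 96 was meant, the wording still misstates the tolerated dropout.

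A reader might go further and infer that the trial is materially underpowered, or that it must recruit 128. The documents do not support either: the loss is about one point against the target, and correcting the statement resolves the inconsistency.

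**Conclusion.** The statement is wrong as written, and the error is minor. With 120 enrolled and 25% lost, 90 remain and omnibus power is about 0.89 instead of 0.90. The shortfall is 6 against the stated 96, or 3 against the minimum of 93. Equivalently, 120 is 8 fewer than the 128 that would keep 96 at that dropout.

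This rests on four assumptions: 0.4 is Cohen's f; the dropout rate applies to those enrolled; the losses are not replaced; and they fall about evenly over the four groups. The power figures concern only the omnibus four-group ANOVA used for the sample size, not any other comparison in the trial.

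**What to change.** Keep 120 and correct the sentence in Sample size estimation in one of two ways:

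- state that 120 allows for 20% dropout, leaving 96 evaluable with power 0.91; or
- keep the 25% and state that 90 then remain evaluable, with power about 0.89.

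Either version makes the printed numbers agree. The cost is one sentence and a slightly less favourable stated dropout allowance or power. Enrolment, allocation and conduct do not change.
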